### Recruitment and duration of the study

The study is expected to last 3 years. After the pulmonary clinical visit all patients who meet the inclusion criteria will be asked to join the study. If they agree to do so they will be asked to sign a form to indicate their informed consent to participate. After this they will undergo psychological assessment (baseline, T0). Follow-up assessments will be carried out 3, 6 and 12 months after recruitment (T1, T2 and T3, respectively) using the same procedure.

### Proposed analyses

Descriptive analyses will be performed for all study variables. We will assess the effect of the interaction between treatment (experimental versus control) and time (three repeated measures) on primary outcome variables (acceptance of treatment; adherence to treatment). Missing data will be imputed with multiple imputation techniques [58, 59].

Before-after differences will be analysed with appropriate within-group tests (paired samples *t* test; Wilcoxon test). Multiple regression will be used to assess the influence of baseline variables on outcome indicators and identify predictor variables.

The analysis will be performed using the intention-to-treat procedure. The significance level will be 5% (*p* ≤ 0.05). Data analysis will be performed using SPSS software.

Data collection and analysis will begin in month 1 and will last for 24 months, i.e. until 1 month after the last follow-up data have been collected.

We will report reasons for withdrawal for each randomisation group and compare the reasons qualitatively. The effect that any missing data might have on results will be assessed via sensitivity analysis of augmented data sets. Dropouts (essentially, participants who withdraw consent for continued follow-up) will be included in the analysis by modern imputation methods for missing data.

For more details about the trial, refer to the SPIRIT Checklist (Additional file 1).

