### Objectives

The primary objective of the study is to evaluate the effects of psychological support on the acceptance of, and adherence to, NIV. Secondary aims include assessment of the change in QoL between baseline and after 3, 6 and 12 months following recruitment, identification of psychological and clinical factors that predict rejection or misuse of NIV, and factors that predict the success of the psychological intervention.

The primary outcome will be a latent variable related to indices of use of NIV equipment and adherence to treatment regime: the effects on change from baseline in acceptance to NIV in COPD patients at 3, 6 and 12 months as measured by weekly means and standard deviations of hours of use of NIV as recorded by the ventilator and changes in adherence defined as the difference between prescribed and effective NIV hours. Change in QoL will also be measured relative to baseline at 3, 6 and 12 months using the EuroQoL (EQ-5D) questionnaire, respiratory, functional and biomedical parameters. Survival rates after starting the adaptation to NIV and psychological variables will be considered as secondary outcomes.

As well as evaluating clinical and psychological variables we will also evaluate econometric outcomes. The study will explore the potential impact of the psychological intervention on the cost to the Italian welfare system of providing health care for patients with COPD. These assessments will be based on standard econometric indices (e.g. quality-adjusted life years (QALYs); DALYs).

Finally, semistructured interviews will be conducted to gain insight into patients’ perceptions of NIV.

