**Fig. 1 Fig1:**
[figure not shown]
Flowchart of the study design

Subjects in the *experimental group* will receive a brief psychological intervention in addition to standard. This will include counselling and psychological support, mindfulness-based cognitive restructuring exercises [40] and relaxation training [41]. The intervention will also include neuropsychological rehabilitation exercises if required; this will be decided on a case-by-case basis, using clinical notes and the Addenbrooke’s Cognitive Examination (ACE-R) and Confusion Assessment Method (CAM) scores. Each patient’s psychological needs will be assessed at the beginning of the psychological intervention, paying special attention to aspects related to the disease (e.g. perception, understanding, awareness of symptoms). Thereafter, the psychological intervention will give more importance to the risks, doubts and fears arising from use of NIV. The intervention will consist of cognitive reframing exercises, relaxation training and, if necessary, neuropsychological rehabilitation exercises. Specifically, these intervention components extend from lowering arousal to providing disease information and management in order to understand better how to cope with NIV and with COPD symptoms, to an emotionally supportive environment in which subjects can address their fears and anxieties, as well as behavioural and cognitive coping strategies. The duration of the intervention will vary from a minimum of four weekly sessions to a maximum of eight according to the needs of the patient. Each session will last about 30–45 min. Sessions will be conducted in a hospital setting, or at the patients’ house or via telemedicine if patients are unable to attend the hospital.

Subjects assigned to the *control group* will spend six sessions watching videos related to the management of their disease (sessions will last about 30 min).

The psychologists who conduct the intervention will be blind to the assessments and vice versa (for the study procedure: schedule of enrolment, interventions and assessments, which reflects the Standard Protocol Items: Recommendations for Interventional Trials (SPIRIT) figure, see Fig. 2).

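### The only between-arm analysis named for the primary outcomes is treatment × time over three measures; if these are months 3, 6 and 12, a lasting benefit is detected only at the 5% error rate

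*Protocol article*

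**What the plan says.** All references are to the protocol article.

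- **Objective (Objectives).** "The primary objective of the study is to evaluate the effects of psychological support on the acceptance of, and adherence to, NIV".
- **Outcome (Objectives).** Acceptance is described as "the effects on change from baseline in acceptance to NIV in COPD patients at 3, 6 and 12 months", taken from hours of use recorded by the ventilator. Adherence is the gap between prescribed and effective hours.
- **Visits (Recruitment and duration of the study).** Baseline comes first: "After this they will undergo psychological assessment (baseline, T0"). Then: "Follow-up assessments will be carried out 3, 6 and 12 months after recruitment (T1, T2 and T3, respectively"). That makes four assessments, three of them after baseline.
- **Intervention (Design and interventions).** "The duration of the intervention will vary from a minimum of four weekly sessions to a maximum of eight", so it would normally be over before the month-3 visit.
- **Analysis (Proposed analyses).** "We will assess the effect of the interaction between treatment (experimental versus control) and time (three repeated measures) on primary outcome variables", namely acceptance and adherence. The neighbouring sentence, "Before-after differences will be analysed with appropriate within-group tests", does not compare the arms, and multiple regression is reserved for the influence of baseline variables and for finding predictors.
- **Sample size.** 128 patients for power 0.80 with t(126), and 172 for power 0.90 with t(170). The target is 150.

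**The concern.** The objective asks whether patients given psychological support use NIV more, and closer to prescription, than controls. A treatment × time interaction over three post-baseline visits asks something else: whether the gap between the arms widens or narrows during follow-up. A gap that is already there at month 3 and stays the same contributes nothing to that test, however large it is.

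With a short intervention given early, a benefit that is present at month 3 and persists is a plausible and desirable result. If the interaction were used to judge the primary outcomes, that result would usually come out non-significant. The sample size calculation has the form of a two-group comparison of means, so the contrast that was powered and the contrast named for analysis are not the same.

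**Working it through.** **Step 1. Which three measures?** Three readings are possible.

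- *T1, T2, T3.* This matches the three follow-ups and the three change-from-baseline values per patient at 3, 6 and 12 months.
- *T0 to T3.* This has four levels, not three.
- *T0 plus two follow-ups.* This has three levels but drops one of the time points in the outcome definition.

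The first fits the document's own count best. The text does not say so outright.

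**Step 2. Reproduce the sample size.** Two-sided two-sample t test, 1:1 allocation (the ratio is not stated), α = 0.05, standardised effect d. Noncentrality = d·√(n/2), with n per arm. The effect size is not given, so d is found from the stated figures.

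- N = 128: solving for power 0.80 gives d = 0.499. With d = 0.5, noncentrality = 0.5·√32 = 2.83, critical t(126) = 1.979, power 0.801.
- N = 172: solving for power 0.90 gives d = 0.497. With d = 0.5, noncentrality = 0.5·√43 = 3.28, critical t(170) = 1.974, power 0.903.

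Both figures are reproduced by a comparison of two means at d = 0.5. At N = 150 the same single-visit comparison has power 0.86.

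**Step 3. Interaction over T1 to T3.** Assume n = 75 per arm, unit variance and equal correlation ρ between visits. With arm differences δ₁, δ₂, δ₃ and mean δ̄, the F test has 2 and 296 df and noncentrality

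λ = (n/2)·Σ(δⱼ − δ̄)² / (1 − ρ).

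For a constant benefit every δⱼ equals δ̄, so λ = 0 and power equals α, whatever d or ρ is. Simulation (4,000 trials per setting, ρ 0.3 to 0.8) gave rejection rates of 0.05 to 0.06 at d = 0.5 and about 0.05 at d = 1.0.

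**Step 4. Arm difference averaged over T1 to T3.** The variance of a patient's mean is (1 + 2ρ)/3. Noncentrality = δ̄·√(n/2)/√((1 + 2ρ)/3), with 148 df. For δ̄ = 0.5:

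- ρ = 0.5: 0.5·√37.5/√0.667 = 3.75, power 0.96
- ρ = 0.6: 0.5·√37.5/√0.733 = 3.58, power 0.94
- ρ = 0.8: 0.5·√37.5/√0.867 = 3.29, power 0.90

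**Step 5. Other shapes of effect, ρ = 0.6.**

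| Arm difference at T1, T2, T3 | λ | Interaction | Averaged difference |
|---|---|---|---|
| 0.5, 0.5, 0.5 | 0 | 5% | 94% |
| 0.5, 0.4, 0.3 | 37.5 × 0.02/0.4 = 1.88 | 21% | 81% |
| 0.5, 0.25, 0 | 37.5 × 0.125/0.4 = 11.7 | 87% | 43% |
| 0, 0.25, 0.5 | 11.7 | 87% | 43% |

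The last two rows are equal because λ depends only on the spread of the differences, not on their order.

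**Step 6. If T0 is a level of time.** On the raw scale the profile is 0, 0.5, 0.5, 0.5. Simulated interaction power is 0.75 at ρ = 0.3, 0.90 at 0.5, 0.99 at 0.7 and about 1.00 at 0.8. A sustained benefit is then detected.

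**The case against.** The strongest reply is that the finding turns on one undefined phrase. The analysis section never identifies the three measures. Step 6 shows that with baseline as a level of time the interaction is an ordinary test of differential change, and the problem goes away. This stands as a limit on the conclusion. It does not rescue the sentence, because T0 to T3 is four assessments, and some correction is needed on either reading.

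Three stronger readings are tempting, and the documents do not support them.

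- *Baseline ventilator data cannot exist, so T0 must be excluded.* The article does not say this. It defines acceptance as change from baseline, which presupposes a baseline value, and the eligibility criteria do not require patients to be new to NIV. The case for T1 to T3 rests on the count of visits and on the change-score definition.
- *The trial will declare no effect when support works.* The article does not call the interaction the primary test, gives no decision rule, and does not say how a null interaction would be read. A model with this interaction normally also contains a treatment term, and a full analysis plan may name it. What can be said is that the published text names no other arm comparison for these outcomes.
- *The test rewards a benefit that fades.* It is equally sensitive to one that grows. The Background notes that adherence to medication falls over time. If NIV use did the same and support slowed the fall, the arms would separate during follow-up and the interaction would pick this up.

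It is also fair to say that an effect largely in place by month 3 is inferred from the length of the intervention; no figure in the article shows it.

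**Conclusion.** The point holds conditionally. On the best-supported reading, the one arm comparison named for the primary outcomes does not address the primary objective and does not match the two-group comparison behind the sample size. For a benefit that is constant from month 3 to month 12, its power equals α, about 5%, against about 90 to 96% for the averaged arm difference. Mild waning leaves it weak (21% against 81%), so the weakness is not confined to an exactly flat profile.

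The 5% figure needs only a constant benefit and time restricted to T1 to T3; it does not depend on effect size, variance or correlation. The 90 to 96% range rests on assumptions: d = 0.5 (implied by both stated sample sizes), 75 per arm, compound symmetry and ρ from 0.5 to 0.8. If T0 is a level of time, the loss of power disappears and what remains is a wrong count of measures.

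**What to change.** In Proposed analyses:

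1. Name the between-arm difference over follow-up as the primary contrast, either averaged over T1, T2 and T3 or at one stated visit. Apply it to both acceptance (hours of use) and adherence (prescribed minus effective hours). This brings the analysis into line with the comparison used for the sample size.
2. State whether T0 is a level of time or a covariate, and make the number of repeated measures agree with that choice.
3. Keep treatment × visit over T1 to T3 as a secondary question on whether the effect lasts.

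A mixed model for repeated measures would supply all of these contrasts. Further baseline covariates are optional. The cost is a change of wording: same patients, same visits, same data. The article reports recruitment as ongoing; the change should be made and dated before any comparison of the arms is seen.

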### Subjects and setting

The study will be conducted in a Clinical and Research Centre, HD Respiratory Rehabilitation Unit, Fondazione Don Carlo Gnocchi, IRCCS Santa Maria Nascente, Milan (Italy), a centre chosen based on documentation of, among other things, patient availability.

We aim to recruit 150 patients with COPD who have been recommended to use NIV based on the GOLD criteria (from moderate to severe) [36, 37].

The *inclusion criteria* are as follows: age 18 years or older; inpatients or outpatients; with moderate (GOLD 2–50% ≤ FEV_1_ < 80% predicted) to severe (GOLD 3–30% ≤ FEV_1_ < 50% predicted) COPD.

The *exclusion criteria* are as follows: refusal of consent; pregnancy; oncological history or history of psychiatric/mental disorders, according to *Diagnostic and Statistical Manual of Mental Disorders, fifth edition* (DSM-V) criteria [38, 39], with the exception of anxiety and depression, as indicated in the patient’s clinical record; immunosuppressive disease as the principal condition; stable use of antidepressant drugs.

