### Sample size

Based on statistical analysis, preventive inherent power and sample size [40] we anticipate that the study will require 150 subjects. We will recruit between 128 subjects (statistical power of 0.80; *α* = 0.05; 1 − *β* = 0.80; *t* (126) =1.97) and 172 subjects (statistical power equal to 0.90; *α* = 0.05; 1 − *β* = 0.90; *t* (170) = 1.97). The inherent power also emphasises that such analyses have been carried out using data for a scientific study that have a comparable primary outcome [33].

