### Randomisation

#### Sequence generation

The patients will be randomised through a simple method, extracting a unit from the population using a method which guarantees the causality of the extractions (https://www.random.org).

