#### Medical and clinical assessment

This will cover:NIV use (prescribed hours, effective hours and their difference)The effects on change from baseline in acceptance of NIV in COPD patients as measured by weekly means and standard deviations of hours of use of NIV as recorded by the ventilatorChanges in adherence defined as the difference between prescribed and effective NIV hoursSurvival rate at different time after starting the adaptation to NIV, reported in terms of monthsSimple spirometry: forced expiratory volume in the first second (FEV1); forced vital capacity (FVC); FEV1/FVCFatigue, measured by the Fatigue Severity Scale (FSS) [42]Emogasanalysis (EGA): potential of hydrogen (pH); partial pressure of oxygen in arterial blood (PaO2); partial pressure of carbon dioxide in arterial blood (PaCO2); hydrogen carbonate concentration (HCO3)

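### The primary comparison names no baseline covariate, so it may give up precision on the between-arm difference that already collected baseline values could supply.

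*Protocol article*

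**What the plan says.** **Primary analysis.** Under Proposed analyses the protocol article says: "We will assess the effect of the interaction between treatment (experimental versus control) and time (three repeated measures) on primary outcome variables". No covariate is attached to this comparison. The same section gives baseline variables another task, a multiple regression to find which of them predict the outcome indicators.

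**Allocation.** Sequence generation says: "The patients will be randomised through a simple method". No stratification or blocking is mentioned.

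**Population.** Subjects and setting admits patients on these terms: "age 18 years or older; inpatients or outpatients". They may have moderate or severe COPD.

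**Sample size.** The section gives two anchors, "We will recruit between 128 subjects (statistical power of 0.80" and "172 subjects (statistical power equal to 0.90", with 126 and 170 degrees of freedom, and the target: "we anticipate that the study will require 150 subjects". It states no effect size.

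**Baseline data.** The Assessment section lists spirometry, blood gases, HADS-A and HADS-D, and the ACE-R. It also lists "NIV use (prescribed hours, effective hours and their difference". The Background reports clinical experience that patients with cognitive deficits, anxiety or depression are less likely to accept NIV. It adds that no study has yet identified the individual psychological factors responsible.

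**The concern.** The trial rests on the idea that a patient's psychological and cognitive state affects how NIV is used. It measures that state at the start, and predicting rejection or misuse is a secondary aim. Yet the main treatment comparison, as described, makes no use of these measurements. Nor does the allocation, since simple randomisation does not balance prognostic factors by design.

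What is at stake is efficiency. If baseline values explain part of the variation in NIV use, adjusting for them narrows the interval for the treatment effect at almost no cost. There is also a reason to settle the matter early. The planned predictor regression draws on the same variables, so covariates added to the treatment comparison later could appear to have been chosen from the results.

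**Working it through.** **Inputs**
- Total sample 128 at power 0.80, 172 at power 0.90, target 150 (Sample size).
- Significance level 0.05 (Sample size and Proposed analyses). Sidedness is not stated in words, but the printed critical value of 1.97 fits a two-sided test: the two-sided values are 1.979 on 126 df and 1.974 on 170 df, against about 1.66 one-sided.
- Assumption: 1:1 allocation, so 75 per arm at 150. The ratio is not stated.
- Assumption: standardised difference d = 0.5. Solving back from the stated figures gives 0.499 at 128 and 0.497 at 172.
- Assumption: covariates explain a share R² of outcome variance between 0 and 0.30. The article gives no correlation or R².

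**Step 1: reproduce the plan's figures.** For a two-sample t test with N patients, the non-centrality is d × √(N/4) on N − 2 df.
- N = 128: 0.5 × √32 = 2.83, power 0.801.
- N = 172: 0.5 × √43 = 3.28, power 0.903.
- N = 150: 0.5 × √37.5 = 3.06, power 0.860.

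The sample size is therefore that of an unadjusted two-group comparison of means, with no credit for covariates.

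**Step 2: gain on the between-arm difference.** Adjustment multiplies the residual variance by (1 − R²). The effective d becomes 0.5/√(1 − R²), the interval width is multiplied by √(1 − R²), and the equivalent unadjusted sample is 150/(1 − R²).

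| R² (assumed) | Effective d | Power at 150 | Interval width ratio | Equivalent unadjusted N |
|---|---|---|---|---|
| 0 | 0.500 | 0.860 | 1.00 | 150 |
| 0.05 | 0.513 | 0.877 | 0.97 | 158 |
| 0.10 | 0.527 | 0.894 | 0.95 | 167 |
| 0.20 | 0.559 | 0.925 | 0.89 | 188 |
| 0.30 | 0.598 | 0.953 | 0.84 | 214 |

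These powers assume that all 150 patients contribute. They ignore the few degrees of freedom spent on the covariates.

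**Step 3: does the gain reach the interaction test?** Suppose patient i at visit j has an outcome containing a term γ·xᵢ, where xᵢ is a baseline value. The interaction compares arms on within-patient differences between visits. In such a difference the term is γ·xᵢ − γ·xᵢ = 0. With complete data, a covariate entered as a main effect therefore leaves the interaction estimate and its standard error unchanged. A simulated example (150 patients, three visits, complete data, one covariate explaining roughly 30% of variance) agrees. The standard error of the arm-by-visit term stayed at 0.1375, while that of the between-arm level difference fell from 0.165 to 0.139. The table in Step 2 thus applies to the level difference only.

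**Step 4: chance imbalance.** With 75 per arm, a factor present in half the patients differs between arms by at least 10 percentage points with probability 22%, and by at least 15 points with probability 6% (exact binomial). These figures describe covariate balance. They do not measure bias in the treatment estimate.

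**The case against.** **The quoted analysis is an interaction, and main-effect covariates do not sharpen it.** This stands. Step 3 confirms it, so the gain requires the between-arm difference to be the declared target. That target agrees with the two-group t test behind the sample size, but the change must be stated openly.

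**Absence of a covariate from a condensed article does not mean exclusion.** This stands in part. The article nowhere rules out covariates, and a fuller document may list them. It does, however, describe both the primary comparison and a separate role for baseline variables, so the point does not rest on silence alone.

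**Prognostic strength is unknown.** This stands. A reader might infer that the baseline variables are strong predictors and that precision is certainly lost. The article gives no figure and says the individual psychological factors are unidentified. The range must therefore include zero.

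**The unadjusted analysis is not wrong.** This stands. A reader might infer that simple randomisation leaves a biased or uncorrected comparison. It does not: the estimator is unbiased over the randomisation, the type I error is valid, and chance imbalance is already reflected in the standard error. With complete data, constant level differences also cancel from the interaction.

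**The change-from-baseline wording already handles some imbalance.** This is partly right, for the outcome's own baseline. Patients are adapting to NIV, so baseline hours may be zero or absent, in which case the subtraction corrects little.

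**Not every obvious covariate is available.** This stands. Inpatient or outpatient status appears as an eligibility term and is not among the listed assessments. Prescribed hours are listed, but not as fixed before allocation, and they are a component of the adherence outcome. Nothing says that they cap the hours used.

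**Conclusion.** The point holds as a recommendation on efficiency; the plan is not in error. The described primary comparison leaves unused some baseline values that the article itself treats as plausibly related to NIV use. Under d = 0.5, 75 analysed patients per arm and R² from 0 to 0.30, adjustment would move power for the between-arm difference from 86% to somewhere between 86% and 95%, and narrow the interval by 0 to 16%. Where in that range the trial would fall cannot be told from the article. The documents do not support a claim of bias, of an inflated error rate, or of greater power for the interaction test.

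**What to change.** Before any comparative data are seen, state the primary model as a repeated-measures model with arm, visit and arm-by-visit. Adjust it for a short list of values recorded before allocation, for example FEV1, PaCO2, HADS-A, HADS-D and ACE-R. Include prescribed NIV hours only if they are fixed before allocation.

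Name the adjusted between-arm difference at the follow-up visits, with its 95% interval, as the primary estimate, and say whether it is averaged over visits or taken at one named visit. State explicitly that this makes the between-arm difference the target, in line with the sample-size calculation. Show the unadjusted result as support, and keep the predictor regression separate.

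The cost is a few sentences, a few degrees of freedom and a rule for missing covariate values. The example covariates are already on the assessment list, and recruitment was still under way when the article was written. If a fuller protocol or SAP already names the covariates and the target, confirming that is enough.

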Patterns of acceptance of non-invasive ventilation (NIV) are examples of the interaction of psychological and physical factors. Despite the fact that NIV can produce significant clinical improvement in their condition, patients often reject it or fail to use it appropriately. NIV rejection or its inappropriate use results in worse clinical outcomes and increased health care costs. Appropriate use of NIV is crucial, given that adherence to medication decreases over time and is inversely related to the number of drugs prescribed [23, 24]. Acceptance and adherence to NIV treatment can reduce hospital admissions and physician visits [25]. Using NIV requires the patient to make some behavioural and lifestyle changes, such as changes in daily routine to allocate time for ventilation, and this may reduce adherence to the treatment [24]. Treatment adherence may also be adversely affected by the use of different drugs and devices, or because patients receive inadequate education about the illness and associated morbidities from their physician [26, 27].

Clinical experience suggests that patients with cognitive deficits [12, 28, 29] or psychological problems, such as anxiety and depression, are less likely to accept and comply with NIV regimes; however, there has been little research on this. The few available studies focussed on early NIV failure (defined as the need for endotracheal intubation or death within 24–48 h of starting NIV) [30, 31], quantifying adherence [32] and largely neglected predictors of nonadherence [33]. No study has identified the individual psychological factors that increase the risk of rejection or improper use of NIV. Previous studies suggest that COPD patients who clearly demonstrated a lower survival benefit from the NIV usage exhibit worse average daily NIV adherence, because of the imbalance between the constraints that NIV imposes and the improvement that patients’ perceive in their condition [34]. Ventilator settings are not easy to adjust and they influence sleep quality, which has spill-over effects on daytime life [34, 35]. The effects of psychological support in promoting the machine’s acceptance have also not been adequately investigated.

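### The multiple-imputation rule does not separate death or rejection of NIV from lost records, so it could bias the comparison of NIV hours in either direction

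*Protocol article*

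**What the plan says.** All the rules on missing data stand in the Proposed analyses section of the protocol article. The general rule is "Missing data will be imputed with multiple imputation techniques". A second sentence covers dropouts: "Dropouts (essentially, participants who withdraw consent for continued follow-up) will be included in the analysis by modern imputation methods for missing data". A third promises a check: "The effect that any missing data might have on results will be assessed via sensitivity analysis of augmented data sets". The section also says "The analysis will be performed using the intention-to-treat procedure" and undertakes to report reasons for withdrawal by group and compare them qualitatively.

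The Objectives section builds the primary outcome from two quantities. Acceptance is measured by "weekly means and standard deviations of hours of use of NIV as recorded by the ventilator". Adherence is measured by "changes in adherence defined as the difference between prescribed and effective NIV hours". Survival is a secondary outcome, and EQ-5D is measured at 3, 6 and 12 months. The Background section says of NIV that "patients often reject it or fail to use it appropriately".

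No section says what value hours of use take after a patient rejects NIV or dies. Equally, no section says that those hours are treated as missing.

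**The concern.** Hours can be absent for three different reasons, and one rule covers them all.

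- **The record is lost, or a living patient withdraws consent.** A true value exists but is not seen. Multiple imputation suits this case, if its assumptions hold.
- **The patient has rejected NIV.** Effective use is 0 h. This is the failure the trial is meant to detect. If the device has gone back or was never taken, the ventilator may supply no record, and the data set may show a blank.
- **The patient has died.** No value exists.

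Standard multiple imputation assumes data are missing at random. Unless rejection is in the imputation model, a blank left by a rejecter is filled from the patients who still supply data, most of whom are users. Patients who reject NIV may also withdraw consent, and that group is named for imputation. For the dead, the rule as worded would generate hours and EQ-5D scores that cannot exist. The Econometric assessment section uses quality-of-life change for QALYs, so invented EQ-5D values could reach the economic results too.

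The primary treatment effect is at stake. Adherence is prescribed minus effective hours, so any error in effective hours passes into it one for one, with the sign reversed.

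**Working it through.** **No stated figure to reproduce.** The article gives no rejection rate, death rate, mean hours or SD. Every input below is therefore an assumption, and a range is shown. Only the total of 150 comes from the Sample size section; 75 per arm assumes equal allocation. The sample size itself is not affected by this point.

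**Set-up.** In an arm, a share *r* rejects NIV (true use 0 h) and the rest average *m* hours. A fraction *f* of rejecters has no record; the others are logged as 0 h. Imputation is within arm and does not use a patient's own earlier hours.

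- True arm mean: (1 − *r*) × *m*
- Arm mean after imputation, equal to the mean of observed patients: (1 − *r*) × *m* / (1 − *r* × *f*)

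**Main case: rejection 30% control and 15% support, *m* = 6 h in both arms.**

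- True difference: 0.85 × 6 − 0.70 × 6 = 5.10 − 4.20 = 0.90 h
- *f* = 0.25: 5.10/0.9625 − 4.20/0.925 = 5.30 − 4.54 = 0.76 h
- *f* = 0.50: 5.10/0.925 − 4.20/0.85 = 5.51 − 4.94 = 0.57 h
- *f* = 1: 5.10/0.85 − 4.20/0.70 = 6 − 6 = 0 h

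**Range.** The same formula gives these differences (support minus control, hours):

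| Rejection, control / support | Users' hours, control / support | True (*f* = 0) | *f* = 0.25 | *f* = 0.50 | *f* = 1 |
|---|---|---|---|---|---|
| 20% / 10% | 6 / 6 | 0.60 | 0.49 | 0.35 | 0 |
| 30% / 15% | 4 / 4 | 0.60 | 0.51 | 0.38 | 0 |
| 30% / 15% | 6 / 6 | 0.90 | 0.76 | 0.57 | 0 |
| 40% / 20% | 6 / 6 | 1.20 | 1.05 | 0.83 | 0 |
| 30% / 15% | 6 / 7 | 1.75 | 1.64 | 1.49 | 1.00 |
| 30% / 28% | 5 / 6 | 0.82 | 0.86 | 0.91 | 1.00 |
| 30% / 30% | 6 / 7 | 0.70 | 0.76 | 0.82 | 1.00 |

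The first five rows shrink and the last two grow. When every rejecter is missing, the result is simply the difference among users.

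**Power in the main case.** With SD 2 h among users, an arm's variance with zeros kept is (1 − *r*)(2² + 6²) − [(1 − *r*) × 6]². That is 28 − 17.64 = 10.36 for control and 34 − 26.01 = 7.99 for support. The standard error is √[(10.36 + 7.99)/75] = 0.495 h. Power is about Φ(0.90/0.495 − 1.976) = Φ(−0.16) = 0.44. A simulation (1,500 trials, 20 imputations within arm, Rubin's rules) also gave about 0.44 with zeros kept. After imputation it gave 0.35 at *f* = 0.25, 0.22 at *f* = 0.50 and 0.06 at *f* = 1. In the equal-rejection case with *f* = 1, power rose from 0.24 to 0.73, because the estimate is inflated and the zeros no longer add to the variance.

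**Death.** No arithmetic is needed. Survival is an outcome, so deaths within follow-up are foreseen, and the general rule sets no limit at death.

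**The case against.** The strongest reply is that the article never calls a rejecter's hours missing. Dropouts are described essentially as people who withdraw consent to follow-up, and rejecting NIV is not the same thing. The Medical and clinical assessment section lists effective hours as an item. A rejecter still in follow-up therefore has an observed 0 h, and intention to treat keeps that patient in. The Objectives section plans to find predictors of rejection, so rejection has to be known. The article is a condensed account, and the full protocol or analysis plan may hold the finer rules.

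Most of this stands, and it rules out three stronger readings:

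- **That rejecters will be given users' hours and the effect erased.** The text does not say so. Reaching 0 h needs every rejecter to be missing and no benefit among users. An imputation model that used earlier hours or recorded rejection could also lessen the bias.
- **That the bias is towards zero whenever support reduces rejection.** This is false. In the 30% / 28% row rejection falls, yet 0.82 h rises to 1.00 h.
- **That the planned sensitivity analysis only re-uses the imputed data.** Its assumptions are not given. It may depart from missing at random, but nothing commits it to do so.

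The reply does not remove the point. The article states a positive rule for missing data and sets no boundary to it. Intention to treat fixes the arm in which a patient is counted, not the value that patient receives. A qualitative comparison of withdrawal reasons does not change the estimate.

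**Conclusion.** The concern holds as a defect in a stated rule that could bias the primary comparison; it is not a demonstrated loss of the treatment effect. Multiple imputation is prescribed without separating death or stopping NIV from lost records, in a trial where both are foreseen and one of them is the failure being measured.

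The size depends on how many rejecters lack a record. If all are logged as 0 h, this source adds no bias. On the assumed inputs, the main case keeps 0.57 to 0.76 h of 0.90 h when 25% to 50% are missing, and nothing when all are. Equal rejection with a benefit among users overstates 0.70 h by up to 0.30 h. The limb on death does not depend on these assumptions: values after death have no meaning under any imputation model.

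**What to change.** In Proposed analyses, or in the analysis plan if it does not already say so, state that:

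1. documented refusal, return of the device or non-use counts as 0 effective hours from that date, as an observed value;
2. no hours or EQ-5D values are imputed after death, and death is handled in one prespecified way. Analysis while alive and a composite that counts death as a poor result are both defensible. The choice between them is a trade-off for the trial team;
3. multiple imputation is done by arm and limited to values truly unobserved while the patient is alive;
4. the planned sensitivity analysis includes a delta adjustment towards lower use.

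The cost is small: a little more analysis work, and recording the date and reason the device was stopped or returned. Reasons for withdrawal are already to be reported. The Trial status section says recruitment is ongoing, so the rules can still be fixed before the final analysis.
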